#### Interim analysis

One interim analysis will be performed after the inclusion of 592 patients (296 per arm). The interim analysis will assess the superiority of the experimental arm versus the control group for the primary endpoint: early termination will be considered only if superiority is met. The interim analysis will have a two-sided alpha level of 0.0003. According to the O’Brien-Fleming spending rule [37], this will leave a two-sided alpha level of 0.049 for the final analysis. The data safety monitoring board will decide if the trial should be stopped according to the results of the interim analysis.

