### Objectives

The primary objective is to assess the impact of a flash dose of preoperative corticosteroids versus placebo on the onset of major complications (Clavien-Dindo > 2) [35] within 30 days after elective curative-intent surgery for digestive cancer.

Secondary objectives are to assess the safety of a preoperative flash of corticosteroids versus placebo and its influence on postoperative and intra-abdominal infections at D30, hospital length of stay and 3-year overall and disease-free survival.

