### Statistical analysis and sample size

This study is a phase III multi center randomized double blind placebo-controlled trial. According to the literature, the incidence of major complications at D30 after surgery is 26% [36]. We hypothesized this proportion will decrease to 18% in patients with corticosteroids administration. Based on these hypotheses with an alpha risk of 5% and a power of 90% and including an interim analysis at the half of the inclusions, 1184 analyzable patients (592 per arm) are required. Allowing for 5% of drop-out, 1200 patients (600 per arm) will be included. Statistical analyses will be performed at the coordinating center (INSERM CIC 1432 of Dijon).

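### The interim rule ties early termination to superiority alone, so as worded it gives no route to considering a stop if major complications are more frequent on corticosteroids

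*Protocol article*

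**What the plan says.** The Interim analysis section of the protocol article fixes four things.

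- Timing: "One interim analysis will be performed after the inclusion of 592 patients (296 per arm").
- Purpose: "The interim analysis will assess the superiority of the experimental arm versus the control group for the primary endpoint".
- Action, in the same sentence after a colon: "early termination will be considered only if superiority is met".
- Decision-maker: "The data safety monitoring board will decide if the trial should be stopped according to the results of the interim analysis".

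The level is two-sided: "The interim analysis will have a two-sided alpha level of 0.0003", and "this will leave a two-sided alpha level of 0.049 for the final analysis".

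The Endpoints section defines the primary endpoint as the frequency of patients with a complication above Clavien-Dindo grade 2 within 30 days of surgery. The Objectives section adds: "Secondary objectives are to assess the safety of a preoperative flash of corticosteroids versus placebo".

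**The concern.** Had the article said nothing about harm, the gap could be left to the full protocol or the board's charter and there would be nothing to raise. Here the text makes a positive statement. The word *only* limits the interim results that open the question of stopping to a single one, superiority.

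The endpoint compared at that look is major postoperative complications, so a harmful effect of the drug would show there directly. If the sentence is followed literally, the board would see an unfavourable unblinded comparison and the interim rule would give it no route to considering termination. At stake are the patients still to be enrolled, and whether the board's role is clear at the moment it matters most.

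**Working it through.** The point is one of wording, so no figure decides it. The arithmetic shows what the sentence leaves out and what the change would cost.

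**The plan's own figures.** Statistical analysis and sample size gives 1184 analyzable patients and an interim at half of inclusions: 1184 / 2 = 592, or 296 per arm, as stated. The assumed rates are 26% (control) and 18% (corticosteroids).

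**Which level to use.** The stated interim level is 0.0003. An O'Brien-Fleming-type spending function at half the information gives 4 × [1 − Φ(2.2414 / √0.5)] = 0.00305, which leaves 0.0490 for the final analysis. The stated 0.049 therefore fits about 0.003. That mismatch is a separate point, so both levels are shown.

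**What the two sides of the test look like.** Assume the control arm runs at the planned rate: 0.26 × 296 ≈ 77 events. With z = (x₁ − x₀)/n ÷ √[p̄(1 − p̄) × 2/n], n = 296 and x₀ = 77, the first counts on the corticosteroid arm to reach the critical value are:

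| Two-sided level | Critical z | Benefit side | Harm side |
|---|---|---|---|
| 0.0003 | 3.615 | 41/296 (13.9%), z = −3.70 | 119/296 (40.2%), z = 3.67 |
| 0.003 | 2.968 | 47/296 (15.9%), z = −3.03 | 111/296 (37.5%), z = 3.00 |

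As written, the results in the third column lead to termination being considered and those in the fourth do not. At 0.0003 the harm-side result is an excess of 42 events, or 14.2 percentage points.

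**Other provisions that might supply the route.**

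- Blinding process allows the blind to be lifted after particular events (unexplained or possible toxic death, certain serious adverse events, suspected unexpected serious reactions). This concerns single patients, not the trial.
- Secondary analysis compares adverse events between arms but states no interim timing and no action.
- Objectives names safety as an aim without linking it to the interim.

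None of these provides a way to act on an unfavourable comparison of the primary endpoint.

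**Patients enrolled after the interim number.** 1200 − 592 = 608; with 1:1 allocation, 608 / 2 = 304 on corticosteroids. This is an upper figure for what a stop could spare, since enrolment may continue while the 30-day outcomes mature.

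**Cost of a non-binding harm guideline.**

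- No true effect: the chance of a false flag is half the two-sided level, i.e. 0.05 / 2 = 2.5% or 0.003 / 2 = 0.15%.
- Planned effect (26% v 18%), nominal 0.05: SE under the null = √(2 × 0.22 × 0.78 / 296) = 0.03405; SE under the alternative = √[(0.26 × 0.74 + 0.18 × 0.82) / 296] = 0.03389. Φ[(−0.08 − 1.96 × 0.03405) / 0.03389] = Φ(−4.33) ≈ 7.5 × 10⁻⁶. The power cost is negligible.

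**How often a true harm would be flagged.** This depends almost wholly on the threshold. For an assumed true rate of 34% against 26%, the SEs are 0.03767 and 0.03752, and Φ[(0.08 − z × 0.03767) / 0.03752] gives about 57% at 0.05, 20% at 0.003 and 7% at 0.0003. The 34% and the 0.05 guideline are illustrations and appear nowhere in the protocol.

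**The case against.** The clause follows a colon after a statement that the look tests superiority. Its natural purpose is to say that the trial may stop early for efficacy and not for futility, which is a common design. It does not define the board's whole safety remit, and the same section leaves the stopping decision to a board named for safety. A charter and a safety stopping procedure are usual matters for the full protocol, so their absence from a condensed article is no finding.

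Most of this stands, and it limits the point in two ways.

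- A reader might infer that the board could not stop the trial for harm. The documents do not support that. Nothing shown forbids the board to recommend stopping on safety grounds, and a charter not shown may provide for it.
- A reader might infer that a two-sided level with action in one direction only is inconsistent. It is not. It amounts to a one-sided test at half the level and is conservative for a false efficacy claim.

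What the objection does not remove is the word *only*. The board decides according to the interim results, and the preceding sentence says which of those results opens the decision. If a charter gives a wider remit, the charter and this sentence disagree and must be reconciled.

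**Conclusion.** The point holds as a defect of wording in a rule that the article states. The interim rule gives no route to considering termination when major complications are clearly more frequent on corticosteroids, although the endpoint is safety-relevant, safety is a stated objective and a safety board receives the comparison. It does not show that the board is powerless or that the two-sided level is misused.

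The size is up to about 608 further patients, some 304 on corticosteroids, given 1200 inclusions and 1:1 allocation. No probability of missed harm can be attached to the plan, because any such figure rests on a harm rate and threshold that the protocol does not give. The correction is cheap and bears on patient safety, so it should be made while the trial recruits; the article expects recruitment to finish in September 2026.

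**What to change.** Limit the restriction to efficacy. In substance: early termination for efficacy requires crossing the superiority boundary at the interim; this does not restrict the data safety monitoring board from recommending that the trial stop for harm, under a non-binding guideline in its charter that spends no efficacy alpha. Check that the charter, if it already covers this, agrees with the new sentence. Leave the threshold and the outcomes considered to the board.

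The cost is one sentence in the protocol and, if needed, one in the charter. The efficacy levels and the sample size do not change, and the superiority error rate can only fall. The remaining downside is the small chance, calculated above, of an unnecessary flag under no effect, which the board is free to set aside.

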### Randomization

Eligible patients will be identified at the preoperative consultation with the surgeon. If the patient meets the eligible criteria, the investigating doctor will present the study. The patient will have a reflection period after the consultation and will be informed of his/her right to withdraw consent at any time without prejudice and without having to justify this decision. After receiving the written informed consent and after verification of the inclusion criteria, the patient will be included.

Patients will be randomized in a 1:1 ratio between 2 groups receiving either 20 mg/kg of intravenous methylprednisolone (experimental group) or an identical-aspect intravenous placebo (control group) at the time of anesthesia induction.

Randomization will be performed online by the investigator using the secure CleanWeb platform at the time of inclusion and stratified on the center, the site of surgery (upper digestive/pancreatic or colorectal cancer) and the surgical approach (scheduled laparoscopic or open surgery).

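### The interim alpha of 0.0003 does not follow from O'Brien-Fleming spending at half information, which gives 0.003 and is the value that pairs with the stated final 0.049

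*Protocol article*

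**What the plan says.** The protocol article, under Interim analysis, fixes four things about the single planned look:

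- **Timing:** "One interim analysis will be performed after the inclusion of 592 patients (296 per arm"). Under Statistical analysis and sample size, the design is described as "with an alpha risk of 5% and a power of 90% and including an interim analysis at the half of the inclusions, 1184 analyzable patients", so the look falls at half of the planned information.
- **Purpose:** efficacy only, since "early termination will be considered only if superiority is met".
- **Interim level:** "The interim analysis will have a two-sided alpha level of 0.0003".
- **Final level:** under the O'Brien-Fleming spending rule, "this will leave a two-sided alpha level of 0.049 for the final analysis".

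The decision to stop is given to the data safety monitoring board on the basis of this analysis. No other part of the article gives a different level or rule.

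**The concern.** The named rule, the information fraction, the interim level and the final level are not independent. Once the rule, the fraction and the overall 5% are set, both levels follow. The printed final level is the one the rule produces at half information, and the printed interim level is not.

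This is the only efficacy stopping threshold the article states. If the interim p-value fell between 0.0003 and 0.003, the result would cross the boundary of the named rule but miss the printed number. The board would then have to choose between them with unblinded results in hand, which a pre-specified boundary is meant to prevent.

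A smaller point concerns timing. The look is tied to inclusion. According to the Randomization section, patients are randomised at inclusion, before surgery, and the primary endpoint needs 30 postoperative days. If the data were cut when the 592nd patient was included, the information would be below the 50% that the boundary assumes.

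**Working it through.** **Inputs, all from the protocol article.** Overall two-sided alpha 0.05; 1184 analysable patients (592 per arm); one look at 592 (296 per arm); major-complication risk 26% under control and 18% under corticosteroids; 1:1 allocation. Information fraction t = 592/1184 = 0.50.

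**1. Levels under the named rule.** The O'Brien-Fleming-type (Lan-DeMets) spending function, applied symmetrically to each side, is

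α(t) = 4 × [1 − Φ(z₀.₉₈₇₅ / √t)].

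At t = 0.50: 2.2414/√0.5 = 3.1698, and 4 × 0.000763 = **0.00305** (|z| = 2.963). The final level is solved from the bivariate normal distribution of the two test statistics (correlation √0.5) so that the overall two-sided error is 0.05. The result is |z| = 1.969, or **0.0490**. The article's final level is thus reproduced exactly, with 0.003 as its partner.

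**2. Can 0.0003 be reproduced?** No variant tried gives it at t = 0.50:

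| Rule at half information | Interim | Final |
|---|---|---|
| O'Brien-Fleming-type spending, each side | 0.00305 | 0.0490 |
| Spending form 2 × [1 − Φ(z₀.₉₇₅/√t)] | 0.0056 | 0.0478 |
| Classical O'Brien-Fleming boundary | 0.0052 | 0.0480 |
| Haybittle-Peto with 0.001 | 0.001 | 0.0498 |
| 0.0003 imposed, final solved for 0.05 | 0.0003 | 0.04996 |

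The first spending function would spend only 0.0003 at t of about 0.35, and the second at about 0.29. The discrepancy is 0.00305/0.0003 = 10.2-fold.

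**3. Overall type I error.** The printed pair (0.0003, 0.049) gives 0.0490. The pair (0.00305, 0.049) gives 0.0500. About 0.001 of the alpha is left unused.

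**4. Effect on the interim decision.** With 296 per arm and a pooled risk of (0.26 + 0.18)/2 = 0.22, the null standard error is √(2 × 0.22 × 0.78/296) = 0.03405. Under the alternative it is √[(0.26 × 0.74 + 0.18 × 0.82)/296] = 0.03389.

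- At 0.0003: difference needed = 3.615 × 0.03405 = 0.123. Crossing probability = Φ[(0.08 − 0.1231)/0.03389] = **0.102**.
- At 0.003: difference needed = 2.968 × 0.03405 = 0.101. Crossing probability = Φ[(0.08 − 0.1011)/0.03389] = **0.267**.

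**5. Overall power** with 592 per arm under 26% versus 18%: 91.46% for the printed pair and 91.51% for (0.00305, 0.049).

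**6. Timing.** The article gives 1200 patients recruited from July 2019 to September 2026, about 86 months, or roughly 14 a month. The lag from inclusion to available 30-day data is not given. If it is assumed to be 2 to 3 months, 28 to 42 of the 592 would lack the endpoint at the moment of the 592nd inclusion, so t = 550/1184 to 564/1184, about 0.46 to 0.48. The spending function there gives about 0.0019 to 0.0024, still six to eight times 0.0003. Timing does not explain the printed figure.

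**The case against.** The strongest reply is that this is a misprint with little consequence. The rule, the fraction and the final level all agree and point to 0.003, so a reader can infer the intended value. The error is conservative: overall type I error stays below 5%, power differs by 0.05 points, and neither the sample size nor the final test is affected. The full protocol and the board's charter are not shown and may carry the right number. This is fair as to size, and a misprint is the likeliest explanation. It also means that the threshold the board would actually apply cannot be known from the article. It does not remove the error: the article gives an explicit threshold that contradicts the rule it cites, on the figure that decides early stopping.

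A second reply is that 0.003 is not the only O'Brien-Fleming value, since the classical boundary gives 0.0052 with 0.0480. That is correct. But the article speaks of a spending rule and gives 0.049, and both indicate the spending-function form. The classical boundary matches neither printed level.

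A third reply is that an analysis performed after 592 inclusions can wait for those patients' 30-day data, and that the data cut is normally left to the SAP or charter. This largely stands. The lag is an assumption, and the effect on error is negligible: at t = 0.46, (0.003, 0.049) gives 0.0501. The timing remark is a clarification and does not carry the finding.

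**Conclusion.** The interim level is wrong as written. With one look at half information, an overall two-sided alpha of 0.05 and O'Brien-Fleming-type spending, the interim level is 0.00305, so 0.0003 and 0.049 cannot both come from the stated rule. Taken literally, the printed threshold cuts the chance of a legitimate early stop from about 27% to about 10% and raises the observed difference required by about 2.2 points. These figures assume the design risks of 26% and 18% and complete endpoint data on 296 patients per arm. The validity of the final analysis is not threatened. What is lost is a single, reproducible stopping boundary, and it should be restored before any interim result is seen.

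**What to change.** State a two-sided interim level of 0.003 (0.00305) with 0.049 for the final analysis, and name the Lan-DeMets O'Brien-Fleming-type spending function so that the pair can be reproduced. This restores the overall error to 0.0500.

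If 0.0003 is deliberate, remove the O'Brien-Fleming attribution and give the final level as 0.0499, which is the exact 0.04996 rounded down. Using 0.0500 would give an overall error of 0.05004.

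In the same sentence, say that the look takes place once 592 randomised patients have completed their 30-day assessment, and that the boundary will be recomputed from the spending function at the information fraction actually reached.

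The cost is one corrected number and one sentence, carried consistently through the protocol, the SAP and the board's charter. No extra patients are needed.

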#### Main analysis

The main analysis will be conducted on intention-to-treat (ITT) analysis. The proportion of patients with postoperative major complications at D30 will be compared using Chi-square test. If there are any differences between the two groups concerning the baseline characteristics, a logistic regression analysis including confounding factors will allow us to check the robustness of the conclusion based on the main analysis. Patients with missing data on adjustment variables will be excluded from multivariate analysis. Results will be expressed using Odds ratios and their 95% confidence intervals. Patients lost to follow-up will be first analyzed successively under the maximal bias analysis (postoperative major complications in corticosteroids patients and no major complications in placebo patients) and then excluded. This ITT analysis will be completed with an m-ITT analysis (exclusion of all subjects in the ITT population who don’t meet inclusion and non-inclusion criteria) and with a per-protocol (PP) analysis (exclusion of all subjects in the ITT population who meet any of the following criteria: no study treatment administered or major protocol deviation).

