#### Secondary analysis

The frequency of patients with postoperative infections and intra-abdominal infections will be compared between groups according to the same strategy as the main analysis (bivariate comparisons using Chi-square, multivariate analysis using logistic regression). The number of days without hospitalization at D30 will be expressed as means +/- SD or as medians (IQR) as appropriate. The Kaplan Meir methods will be used to estimate the overall and the disease-free survival curves. The corresponding survival rates will be calculated at 3 years. Median survival will also be calculated and differences between survival curves assessed using log rank test. A Cox regression analysis will be used to assess the impact of potential prognostic factors on overall survival and disease-free survival at 3 years. Subgroup analyses according to the stratification groups (site of surgery, surgical approach) will be performed for exploratory purposes. Descriptive statistics will be used to summarize adverse events and compared between the two groups. Safety analyses will be performed on the safety population which will comprise all randomized patients who consented to participate in the study and who have been given a treatment.

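### Randomisation is stratified by centre, site and approach, but the primary test is an unstratified chi-square: mildly conservative, with a little power forgone, if the strata are prognostic

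*Protocol article*

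**What the plan says.** All references are to the Protocol article.

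- **Randomization:** allocation is 1:1 and "stratified on the center, the site of surgery (upper digestive/pancreatic or colorectal cancer) and the surgical approach (scheduled laparoscopic or open surgery").
- **Main analysis:** the primary test is named outright: "The proportion of patients with postoperative major complications at D30 will be compared using Chi-square test". Adjustment depends on what is observed: "If there are any differences between the two groups concerning the baseline characteristics, a logistic regression analysis including confounding factors will allow us to check". This model is only a robustness check on the main conclusion. The covariates are not named, and the stratification factors are not mentioned.
- **Secondary analysis:** both infection endpoints are compared "according to the same strategy as the main analysis (bivariate comparisons using Chi-square, multivariate analysis using logistic regression"). The stratification factors appear only here: "Subgroup analyses according to the stratification groups (site of surgery, surgical approach) will be performed for exploratory purposes". Centre is not used even in that way.
- **Statistical analysis and sample size:** "the incidence of major complications at D30 after surgery is 26"%, and "We hypothesized this proportion will decrease to 18% in patients with corticosteroids administration". This is planned at 5% alpha and 90% power with one interim analysis, giving 1184 analysable patients (592 per arm).
- **Interim analysis:** the two-sided level left for the final analysis is 0.049.

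**The concern.** Stratified randomisation keeps the arms balanced on the strata, so chance differences between arms in centre, site and approach no longer add to the sampling variance of the treatment difference. The pooled chi-square variance does not know this. It uses the total outcome variance, including the part between strata. If the strata predict the outcome, that variance is too large, the test rejects too rarely under the null, and some power is given up.

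The trigger for adjustment does not help. It waits for an observed baseline difference, and the design makes such a difference unlikely on exactly these factors. It also makes the choice of adjusted model depend on the data.

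This is not a detail left to an analysis plan. The protocol itself states the test and the condition for adjusting. At stake is a modest loss of efficiency on the primary endpoint and both infection endpoints.

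**Working it through.** **1. The plan's own sample size.** Inputs from the sample size section: p₁ = 0.26, p₂ = 0.18, mean 0.22, difference 0.08, power 90% (z = 1.2816). For two-sided 0.049, z = 1.9686.

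- Without continuity correction: n = [1.9686·√(2·0.22·0.78) + 1.2816·√(0.26·0.74 + 0.18·0.82)]² / 0.08² = (1.1533 + 0.7473)² / 0.0064 = 564.4, so 565 per arm (1130 in total).
- With continuity correction: n′ = (n/4)·[1 + √(1 + 4/(n·0.08))]² = 589.1, so 590 per arm (1180 in total). At 0.05 the same formula gives 587 per arm (1174).

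The stated 1184 is therefore matched closely by a continuity-corrected, unstratified comparison. The 90% power was planned for a test of this kind.

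**2. Expected size of the chi-square under the null.** Let ρ be the share of outcome variance that lies between strata. With balance inside strata, the chi-square's z statistic has variance of about 1 − ρ, so its true size is about 2·Φ(−1.969/√(1 − ρ)). Stratum rates are assumed, with mean 26% and total variance 0.26·0.74 = 0.1924.

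- Two equal strata at 34% and 18%: ρ = 0.0064/0.1924 = 0.033; 1.969/√0.967 = 2.002; size 4.5%.
- Four equal strata at 42, 30, 20 and 12%: ρ = 0.0126/0.1924 = 0.065; critical value 2.036; size 4.2%.
- ρ = 0.11: critical value 2.087; size 3.7%.

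**3. Simulation.** All runs use 1184 patients. A has 2, 4 or 8 strata with exact balance inside strata. B to E have 23 centres (the number given in the Discussion) × 2 sites × 2 approaches = 92 strata, with blocks of 4. Stratum effects, centre sizes and block size are assumptions. CMH is the Cochran-Mantel-Haenszel test over all strata. Entries are weak / moderate / strong strata, in %.

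| Run | Effect; two-sided level | Size, chi-square | Size, CMH | Power, chi-square | Power, CMH |
|---|---|---|---|---|---|
| A | 8-point difference; 0.049 | 4.4 / 4.2 / 3.6 | 4.8 / 4.9 / 4.8 | 91.6 / 92.1 / 92.8 | 92.1 / 93.0 / 94.3 |
| B | constant odds ratio; 0.05 | 4.5 / 4.3 / 3.9 | 4.7 / 4.6 / 5.0 | 91.2 / 89.3 / 85.8 | 90.8 / 90.2 / 88.5 |
| C | marginal 26% vs 18%, unequal centres; 0.049 | 4.8 / 4.3 / 3.7 | 4.9 / 4.9 / 5.0 | 91.4 / 92.2 / 92.8 | 91.3 / 92.6 / 94.1 |
| D | constant risk ratio 18/26, unequal centres; 0.049 | not run | not run | 90.8 / 91.7 / 92.4 | 90.5 / 91.9 / 93.5 |
| E | two-sided 0.049 | 5.1 / 4.8 / 4.0 | not reported | 91.8 / 91.8 / 92.2 | 91.9 / 92.4 / 93.6 |

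In B the log-odds effects (centre SD / site / approach) were 0.2/0.3/0.3, 0.4/0.6/0.5 and 0.6/1.0/0.8. The null variance of the chi-square z statistic was 0.96, 0.95 and 0.89, so variance is overstated by about 4 to 11%. Monte Carlo error in B is about 0.3 points for size and 0.5 for power; in D it is about 0.5 for power.

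CMH on the four site-by-approach cells alone gave power of 91.5 / 92.6 / 93.6 in C and 91.7 / 92.2 / 92.9 in E.

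**4. Power forgone (CMH minus chi-square).** A: 0.5, 0.9, 1.5. B: −0.4, 0.9, 2.7. C: −0.1, 0.4, 1.3. D: −0.3, 0.2, 1.1. E: 0.1, 0.6, 1.4. The small negative values in B and D are within simulation error.

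**The case against.** The strongest reply is that nothing here threatens validity. That stands: the error is in the conservative direction, and the crude comparison remains unbiased.

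Four stronger readings are tempting, and the document does not support them.

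- **The factors were chosen because they drive major complications.** The Randomization section gives no reason. Centre could be a stratum for logistics, since each centre's pharmacy prepares the infusion bags. If the strata are weakly prognostic, the effect is negligible.
- **Power the trial has paid for is being lost.** The sample size matches an unstratified formula, and the chi-square stays above 90% in every scenario except the moderate and strong ones with a constant odds ratio (89.3% and 85.8%). What is forgone is mostly extra power.
- **The reported confidence intervals are too wide and adjustment would narrow them.** The plan reports odds ratios. A covariate-adjusted logistic model targets a conditional odds ratio, whose standard error on the log scale is generally not smaller than the crude one. Power rises because the estimate moves away from 1.
- **Any stratified method would serve equally.** CMH, a logistic model with a centre random effect and a stratum-adjusted risk difference differ in estimand or assumptions.

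It is also fair to say that an adjusted logistic analysis already exists and that its covariates may be left to the analysis plan. That answers part of the point. It does not make the adjusted analysis primary, and it does not remove the imbalance trigger.

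**Conclusion.** The point holds as a modest matter of efficiency. The protocol stratifies on three factors, fixes a primary test that ignores them, and makes adjustment wait for an imbalance that the design itself makes unlikely for those factors. If the strata predict major complications, the chi-square overstates the variance of the treatment difference.

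The size ranges in the brief rest entirely on assumed stratum effects. The direction is secure; the magnitude is not known from the document. The case for change is that a stratified analysis costs essentially nothing if the strata are weak and gains a point or so if they are strong.

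**What to change.** Before unblinding, prespecify one primary analysis that accounts for the stratification factors. A suitable choice is a Cochran-Mantel-Haenszel test stratified by site and planned approach, with centre included after pooling small centres, reported with the stratum-adjusted risk difference and its confidence interval. Use it at the interim and final analyses, and apply it to both infection endpoints. Drop the imbalance trigger for these factors and keep the crude chi-square as supportive.

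A logistic model with arm, site, approach and a centre random effect is an alternative. Because it targets a conditional odds ratio, the sponsor should choose one estimand and state it.

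The cost is wording only, since the factors are already recorded at randomisation. A pooling rule is needed: 23 × 4 = 92 cells, and 1184/92 is about 13 patients per cell. If the strata turn out to be weakly prognostic, power is essentially unchanged.
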